**Fig. 1 Fig1:**
[figure not shown]
Flow Diagram of Progress through Study Phases

#### Sample size

The target total sample size is 264 older adults based on an effect size of 0.38 for mental functioning (primary outcome) as measured by the Mental Component Summary (MCS) score from the 12-item Medical Outcomes Study Short-Form Health Survey (SF-12) that was observed in the previous Ontario randomized controlled trial (MD = 3.68, SD=9.68, power=80%, two-sided alpha=0.05, 20% attrition) [31]. SAS Version 9.4 (PROC POWER, two-sample t-test for mean difference, equal variance, same sample size per group) was used to calculate the sample size. A total sample size of 264 will require 88 participants per province (44 participants per site).

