#### Randomization design

Randomization procedures will be carried out as described in our previous protocol paper [46]. Briefly, the procedures include random assignment to the groups using a 1:1 allocation ratio, stratified permuted block randomization with the sequence generated by a biostatistician not involved in the recruitment process and with the study sites used as strata, and sequences entered into a centralized web-based randomization service (REDCap Version 11.1.9).

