#### Sample size

Sample size will be maintained despite the loss of one of the Quebec sites due to the Prince Edward Island research team offering to recruit an additional 44 participants.

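### At the stated 20% attrition, the target of 264 gives about 78.5% power rather than 80% for the two-sample t-test used to size the trial (minor)

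*Protocol article*

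**What the plan says.** All the ingredients stand in the Sample size section under Data collection in the protocol article. "The target total sample size is 264 older adults", "based on an effect size of 0.38 for mental functioning (primary outcome"), with the inputs "MD = 3.68, SD=9.68, power=80%, two-sided alpha=0.05, 20% attrition". The software is SAS PROC POWER and the test is given as "two-sample t-test for mean difference, equal variance, same sample size per group". Randomization design confirms equal allocation. The total is then divided across the planned sites: "A total sample size of 264 will require 88 participants per province (44 participants per site").

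The article does not print the number of evaluable participants required before the attrition allowance, nor how the allowance was applied. The Sample size entry under the COVID-19 modifications keeps the same total: "Sample size will be maintained despite the loss of one of the Quebec sites", because the Prince Edward Island team recruits 44 more.

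**The concern.** A sample-size statement that gives the effect, SD, alpha, power, attrition and total can be checked in full, and the parts should agree. An allowance for 20% attrition normally means that 20% of those randomised have no usable 6-month outcome, so the evaluable requirement is divided by 0.8. Multiplying it by 1.2 instead gives a smaller total and leaves fewer evaluable participants than the calculation requires.

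At stake is the accuracy of the stated power for the primary outcome. A reader who repeats the calculation will get 275, not 264. The analysis method, type I error and bias are not affected.

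**Working it through.** **Inputs** (all from the Sample size section): mean difference 3.68; SD 9.68; two-sided alpha 0.05; power 80%; attrition 20%; two-sample t-test with equal variances and equal groups.

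**Effect size.** d = 3.68/9.68 = 0.380, which agrees with the stated 0.38.

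**Evaluable number.** Solving the noncentral-t power equation for 80% power gives 109.58 per arm, rounded up to 110, so 220 in total. Power is 80.1% at 110 per arm and 79.8% at 109 per arm.

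**Reproducing the plan's figure.**
- 220 × 1.2 = 264, an exact match.
- 220/(1 − 0.20) = 275, or 138 per arm = 276 with equal arms (46 at each of six sites).

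**Alternatives tried, to see whether 264 can be reached by dividing by 0.8.**
- Normal approximation: 109 per arm, 218 in total; 218/0.8 = 272.5, so 273 (and 218 × 1.2 = 261.6, so 262).
- d = 0.38 in place of 3.68/9.68: again 220, 264 and 275.
- Mean difference and SD varied within their two-decimal rounding: always 220 and 275.
- One-sided alpha 0.05: 87 per arm, 174 in total; neither 174 × 1.2 = 209 nor 174/0.8 = 217.5 is near 264.

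None of these gives 264 by division; only multiplication by 1.2 does.

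**What 264 delivers.**
- Evaluable after 20% loss: 264 × 0.8 = 211.2, about 211, which is 9 short of 220.
- t-test power for a difference of 3.68: 78.5% with 106 and 105 evaluable per arm, 78.3% with 105 and 105.
- Largest attrition that still leaves 220: 1 − 220/264 = 16.7%.
- Difference detectable with 80% power at 211 evaluable (105.5 per arm): d = 0.3875, and 0.3875 × 9.68 = 3.75 points, against 3.68 planned.

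**Possible recovery through ANCOVA.** Suppose 9.68 is the SD of the analysed variable before adjustment, and let r be its correlation with the baseline value. Adjustment reduces the residual variance by the factor 1 − r². The unrounded requirement is 2 × 109.58 = 219.2, so 211.2 evaluable suffice when 1 − r² ≤ 211.2/219.2 = 0.964, that is r² ≥ 0.036, or r of about 0.19 or more. Power at about 211 evaluable would then be:

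| Assumed r | Power |
|---|---|
| 0.20 | 80.1% |
| 0.30 | 82.2% |
| 0.40 | 85.1% |

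The values of r are assumptions; the article gives none.

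**The case against.** **The effect is very small.** This stands. About 1.5 points of power is little when the mean difference and SD both come from one previous trial. An SD of 9.50 instead of 9.68, 1.9% smaller, would restore 80%. The point cannot carry more than a minor rating.

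**The multiplication is inferred.** This also stands. Neither 220 nor the inflation step is printed. If the authors meant a 20% addition to the evaluable number, 264 is computed correctly and the label is loose, since such an addition covers 16.7% loss. The inconsistency does not depend on the mechanism, however: by whatever route 264 was reached, 264 with 20% lost leaves about 211, and the stated inputs need 220.

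**The primary analysis is ANCOVA, not a t-test.** A reader might infer that the trial's primary analysis is underpowered. The article does not support that. The effectiveness analysis section plans ANCOVA on the 6-month change with the baseline value as covariate, and a correlation of about 0.2 would bring power back to 80%. Equally, this does not repair the stated calculation: the sizing uses an unadjusted t-test, takes no credit for the covariate, reports no correlation, and does not say whether 9.68 is already a change-score or adjusted SD.

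**Multiple imputation keeps everyone in the analysis.** It retains all randomised participants, but imputing from baseline and group does not supply the missing 6-month information. The attrition allowance itself treats those outcomes as lost.

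**The COVID-19 section repeats the error.** A reader might count the retained total as a second mistake. It is not one. That entry says only that the planned number is kept by replacing 44 participants, which agrees with 44 per site, and it makes no claim about power or attrition.

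**The article condenses a fuller protocol.** That would excuse an omission. Here the inputs and the result are both printed, and they disagree.

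**Conclusion.** Wrong as written, and minor. The total of 264, 80% power and 20% attrition cannot all hold for the two-sample t-test that the article names. At 264 randomised and 20% attrition, about 211 are evaluable and power is about 78.5%. For 80% power, either attrition must be no more than 16.7%, or the total must be 275 (276 with equal arms).

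The conclusion uses only the article's own inputs and the usual reading of 20% attrition as a share of those randomised. That 264 arose as 220 × 1.2 is a strong inference from an exact match, not a quoted fact. The shortfall applies to the unadjusted t-test used for sizing; the power of the planned ANCOVA cannot be determined from the article and may well reach 80%.

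**What to change.** Keep 264 and correct the sentence in the Sample size section in one of two ways:

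- Restate the power: with 264 randomised and 20% attrition, about 211 are evaluable, giving about 78% power for a mean difference of 3.68 (80% for 3.75) by two-sample t-test.
- Restate the allowance: 264 leaves the required 220 evaluable if attrition is no more than 16.7%.

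It would also help to print the evaluable requirement of 220. If the authors wish to rely on the ANCOVA, they should state the assumed baseline correlation and what 9.68 is the SD of. Only a continued claim of 80% t-test power at 20% attrition would require the target to read 275 (276).

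The cost is one sentence and a slightly less favourable stated figure. No extra recruitment is required, and the COVID-19 section needs no change of its own.

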#### Recruitment and retention

Staff from each of the primary care or diabetes education program sites will be trained to identify potential clients using existing medical records or electronic databases (e.g., electronic medical records) based on the study inclusion criteria. They will then contact potential clients by telephone to determine their interest in learning more about the study and use a standardized script to introduce the clients to the study and screen for study eligibility. Recruitment of vulnerable older adults who have multiple chronic conditions has been challenging in our own research and that of others [62, 63], thus staff that are recruiting at each site will use a clear communication strategy to share information with potential participants related to the study purpose, benefits and risks, and what is being asked of them. Eligible clients who agree to be contacted will then receive a telephone call from a study RA who will share information about the study and arrange a time for the baseline assessment. Written or audio-recorded oral informed consent will be obtained by the RA at the baseline assessment. At the baseline assessment, clients will be asked to invite their family or friend caregiver (aged ≥18 years who provides physical, emotional, or financial care) to participate in the study and provide their contact information. While participation of caregivers is encouraged, it is not required.

Those who agree to participate in the study may be more receptive to the intervention, creating sampling bias. The extent of non-response bias will be assessed by comparing baseline characteristics of those who agree and those who decline to participate in the study.

In relation to retention of study participants, the RC will mail a reminder letter to the participant three months prior to the T2 interview to remind them of the date and time of the interview with the RA. The RA will call the participant three business days prior to their T2 interview to confirm their interview time. At the participant’s request, the RA will also call the participant the day before the interview.

#### Randomization design

Randomization procedures will be carried out as described in our previous protocol paper [46]. Briefly, the procedures include random assignment to the groups using a 1:1 allocation ratio, stratified permuted block randomization with the sequence generated by a biostatistician not involved in the recruitment process and with the study sites used as strata, and sequences entered into a centralized web-based randomization service (REDCap Version 11.1.9).

#### Blinding

Participants will be blinded to their group allocation. Efforts will be made to blind the RAs who conduct the T1 and T2 interviews to group allocation, although this may be difficult to maintain in all cases (e.g., if a client refers to a home/telephone visit or group wellness education session during the interview). The statistician/data analyst will be blinded to group allocation of the participants. The intervention will be known to the providers who are administering the intervention however, they will be unaware of the outcomes being studied. Upon completion of the study, participants will receive a debriefing letter describing the two groups and their group allocation.

### Intervention arm

Key features of the intervention and control arms of the study are outlined in Additional File 2 of our previous protocol paper [46], with further details provided below.

#### Theoretical foundation

In developing complex interventions, it is important to ground them in theories that support effectiveness [53]. Bandura’s social cognitive theory [24, 25] underpins the ACHRU-CPP, consistent with many diabetes prevention/treatment interventions. The previous protocol paper discussed how the constructs in this theory relate to the principles and components of the intervention tested in this trial [46].

#### Intervention development and testing

The intervention was developed in collaboration with older adults with diabetes, caregivers, providers, and researchers [30]. The feasibility, acceptability, and preliminary effectiveness of the ACHRU-CPP were established through a feasibility study conducted with a diabetes education program in a primary care setting in partnership with a community seniors’ centre [30]. The ACHRU-CPP was adapted based on client and provider feedback, implemented and tested in a pragmatic RCT in four sites in Ontario [31] and three in Alberta, Canada [32].

#### ACHRU-CPP intervention description

Participants randomly assigned to the intervention group will be offered the 6-month intervention in addition to usual healthcare services offered by their primary care setting or local diabetes education program. The intervention will be delivered by an interprofessional team of providers in each site including RNs, RDs/Nutritionists, and a PC from a community partner organization, who may be a kinesiologist or exercise specialist.

The core components of the intervention include: (a) up to three home/telephone visits by the RN and/or the RD/Nutritionist; (b) up to six in-person monthly group wellness sessions that include health education, exercise (gentle progressive physical activity) and informal peer support; (c) ongoing nurse-led care coordination and system navigation to link clients to other health care professionals and community services as needed; (d) ongoing caregiver engagement and support during the home/telephone visits and group wellness sessions; (e) monthly case conferences of the intervention team where the team will discuss and evaluate the client’s plan of care; and (f) collaboration with the primary care team and other specialists as needed. The RN or RD/Nutritionist, with the client’s consent, will complete and send alerts (e.g., medication, depressive symptoms, diabetes complications) to communicate concerns with the primary care physician or other providers.

A care plan will be developed at the beginning of the intervention. The intervention team will collaborate with the client in developing and tailoring a coordinated care plan to meet their individual needs and preferences. The care plan will be documented, outline the goals and actions that will be undertaken to achieve the goals, and a copy of the care plan will be provided to the client and all members of the intervention team. Home/telephone visits are expected to begin within two weeks of allocation to the intervention and prior to the initial group wellness session. Subsequent visits will occur at approximately three and five months, in consultation with the participant. Progress towards achieving the goals identified in the care plan will be discussed at each visit and modified as needed.

#### Intervention implementation strategies

The strategies to be used to implement and monitor the delivery of the intervention at each site were described in the prior protocol paper [46]. Briefly these include provider training, outreach meetings between researchers and the intervention team to discuss progress and address challenges, and routine updates and completion of forms documenting intervention components delivered. Compared to previous trials, implementation strategies will increase the use of online resources and virtual methods to facilitate communication across sites and provinces and address recent challenges related to the pandemic.

### Control arm: usual care

Clients who are randomly assigned to the control group will continue to be offered usual care services through their primary care setting or local diabetes education program. The specific services that comprise usual diabetes care differ within and across provinces in terms of the length and focus of educational sessions, whether classes are strongly recommended versus optional (e.g., foot care, cardiac health, diet and exercise interventions), whether home/telephone visits are offered as part of usual care, access to on-site professionals (e.g., endocrinologist, dietitian, physiotherapist, exercise specialist, pharmacist), connections with support services and community resources, and type of follow-up services available. Details of usual care provided at each site will be carefully documented.

### Effectiveness outcomes, measures, and analyses

The effectiveness of the intervention will be evaluated using several older adult and caregiver-relevant measures. We selected standardized tools and chose measures that had been validated in the target population (where possible). We briefly summarize these measures below, and Table 1 provides the details on each measure including a description, time points collected, and associated methods of analysis.

**Table 1 Tab1:** Effectiveness Outcomes, Measures, Target Population, Timing and Analysis

Variable/Outcome	Measure	Study Group(s)^a^	Timing^b^	Method of Analysis
Mental functioning	Mental component summary (MCS) from SF-12 [64]	CT, CG	T_1_, T_2_	Descriptive analyses T1-T2 (Treatment Effect); ANCOVA, subgroup analyses (sex, number of chronic conditions, province)
Physical functioning	Physical Component Summary (PCS) from SF-12 [64]	CT, CG	T_1_, T_2_	Descriptive analyses T1-T2 (Treatment Effect); ANCOVA
Diabetes self care	Summary of Diabetes Self Care Activities (SDSCA) [65]	CT	T_1_, T_2_	Descriptive analyses T1-T2 (Treatment Effect); ANCOVA
Depressive symptoms	Center for Epidemiological Studies Depression Scale (CES-D-10) [66]	CT, CG	T_1_, T_2_	Descriptive analyses T1-T2 (Treatment Effect); ANCOVA
Anxiety	Generalized Anxiety Disorder 7-item Scale (GAD-7) [67]	CT, CG	T_1_, T_2_	Descriptive analyses T1-T2 (Treatment Effect); ANCOVA
Social support	Duke Social Support Index (DSSI) [68]	CT	T_1_, T_2_	Descriptive analyses T1-T2 (Treatment Effect); ANCOVA
Physical activity	Physical Activity Scale for the Elderly (PASE) [69]	CT	T_1_, T_2_	Descriptive analyses T1-T2 (Treatment Effect); ANCOVA
Activities of daily living/instrumental activities of daily living	Older Americans Resources and Services Multidimensional Functional Assessment Questionnaire Activities of Daily Living/Instrumental Activities of Daily Living (OARS ADL/IADL) [70, 71]	CT	T_1_, T_2_	Descriptive analyses T1-T2 (Treatment Effect); ANCOVA
Eating and nutrition risks	Seniors in the Community: Risk Evaluation for Eating and Nutrition (SCREEN II-AB) [72]	CT	T_1_, T_2_	Descriptive analyses T1-T2 (Treatment Effect); ANCOVA
Food security	Single item from Canadian Longitudinal Study on Aging [73]	CT	T_1_, T_2_	Descriptive analyses
Diabetes-related complications	Self-report of retinopathy, neuropathy, peripheral vascular disease	CT	T_1_, T_2_	Descriptive analyses
Laboratory values	HbA1c, e-GFR, LDL cholesterol	CT	T_1_, T_2_	Descriptive analyses, Inferential statistical analysis of T1-T2 change
Caregiver strain	Modified Caregiver Strain Index (CSI) – 13 items [74]	CG	T_1_, T_2_	Descriptive analyses T1-T2 (Treatment Effect); ANCOVA
Utilization of health and social services and associated costs	Health and Social Services Utilization Inventory (HSSUI) [75, 76]	CT, CG	T_1_, T_2_	Descriptive analyses T1-T2 (treatment Effect); Parametric or non-parametric tests depending on distributional properties of cost data, complete case analysis, Hazard Ratio (95% CI) & Risk Difference (95% CI) for ED visits and hospital admissions
Interprofessional team functioning	Partnership Self-Assessment Tool (PSAT) [77]	INT	3 months and end of intervention	Descriptive analyses
Public and community partner engagement	The Quality Involvement Measure [78] The Patient-Centred Outcomes Research Institute’s Ways of Engaging – Engagement Activity (WE-ENACT) Tool [79] Selected items of the Patient-Centred Outcomes Research Institute’s Engagement Activity Inventory (NET-ENACT) Tool [80]	Public and community research partners	3 months and end of intervention	Descriptive analyses

^a^ Four study groups: CT: client; CG: caregiver; INT: intervention team; Public and community research partners.

^b^ Two time points: T_1_: baseline; T_2_: 6 months after baseline.

^c^ PSAT will be completed by core intervention team (e.g., Registered Nurse, Registered Dietitian/Nutritionist, Program Coordinator)

#### Older adult participant outcomes and measures

The primary outcome is the mental function of the older adult participants as measured by the MCS score from the SF-12 [64]. This measure was chosen because functional status is a patient-reported outcome measure (PROM) recognized as important to a wide range of patients including those receiving self-management interventions targeting chronic conditions [81, 82]. We also found this measure to be responsive to the ACHRU-CPP in our previous trial [31] and mental functioning is linked to self-efficacy and the behaviour change constructs that play a central role in the theory underpinning the intervention. As shown in Table 1, a range of secondary outcome measures are also being assessed to capture physical functioning, activity levels, and limitations; diabetes self-management activities; various mental health outcomes; social support; nutrition risks; and clinical measures representing key diabetes risk factors such as measures of blood sugar control (HbA1c), kidney function (GFR), and cholesterol level (LDL) where available in electronic medical records.

The Health and Social Services Utilization Inventory (HSSUI) [46, 75, 76] will be used to measure the use of health and social services as reported by study participants. The six-month cost data will be derived from the product of the “quantity” data on the HSSUI and 2020-2021 “price” data obtained by our team from provincial databases. The costs of use of health and social services will include costs of intervention-specific services such as home/telephone visits and group wellness sessions.

#### Caregiver outcomes and measures

The effectiveness of the intervention on caregiver participants will be assessed on a range of outcomes including mental functioning, physical functioning, mental health, caregiver strain, and self-reported use of acute care services (EDs and hospitals) (See Table 1).

#### Analysis: effectiveness evaluation (older adult and caregiver participants)

The baseline demographic and clinical characteristics of participants who completed both the baseline and 6-month assessments will be compared. Descriptive statistical analysis will be used to summarize outcome variables at baseline and 6 months. For continuous variables, means and standard deviations will be calculated, and for categorical variables, frequencies and proportions will be assessed. Analysis of covariance (ANCOVA) will be used to test the differences in outcome variables between the intervention and control group at 6 months. Separate ANCOVA models will be run for each primary and secondary outcome, with the 6-month change in the outcome as the dependent variable, group (intervention, control) as the independent variable, and the baseline value of the outcome as the covariate.

Statistical tests will use a 0.05 two-tailed level of significance and 95% confidence levels. An intention-to-treat (ITT) approach unadjusted for baseline characteristics will represent the primary analysis, using multiple imputation for missing data. Costs will be applied to the health and social service use reported by clients and caregivers. Group differences in the 6-month change in service use costs will be examined using parametric or non-parametric methods, depending on the distributional properties of the cost data [83].

Sensitivity analyses will be conducted to test the robustness of the results for the primary outcome to various assumptions and analytical approaches used in the primary analyses [84]. A complete case analysis will be conducted to provide a comparison to the ITT results obtained using multiple imputation. A multivariable analysis that adjusts for residual baseline imbalances will be conducted to assess their impact on the effect estimates, if significant imbalances between groups exist post-randomization [85]. As a multi-site RCT, there exists the possibility that participants within a site may be more homogeneous compared to those from another site, thus a sensitivity analysis will be conducted that includes site as a covariate. Distributional assumptions underlying the ANCOVA model will be tested, with non-parametric methods explored if significant violations are present [86]. Since some participants in the intervention group were not offered the full intervention or did not receive any of the intervention (e.g., resulting from choice, due to COVID-related issues), we will conduct an analysis that excludes participants in the intervention group that did not receive any of the intervention for comparison with the results from the primary analysis (which include participants irrespective of whether they received the intervention or not). Finally, exploratory subgroup “sensitivity” analyses will be conducted to assess the potential benefit of the intervention for clinically-meaningful subgroups. The guidance from the recently-published Instrument for assessing the Credibility of Effect Modification Analyses (ICEMAN) [87] was reviewed in an effort to maximize the credibility of the subgroup analysis (if undertaken). The following three factors were pre-selected for the subgroup analysis: sex, number of chronic conditions, and province. We hypothesize that the intervention will be more effective in men because they typically engage in fewer self-management activities and access health care services less frequently than women [88]. We expect the intervention will be less effective in those with a higher number of chronic conditions because of the likelihood that they would have more complex care needs. We also expect to see variation in intervention effects across provinces due to contextual differences (e.g., health care systems, culture, rurality). Regression using two-way interactions between the study group (intervention versus control) and each characteristic will be conducted to determine subgroup effects [89, 90]. It is important to note that the subgroup “sensitivity” analyses will be regarded as exploratory, given the potential for the overall type I error to be inflated [86].

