### Data collection

#### Participant flow, assessments, and timeline

RAs will conduct two assessments (home or telephone interview) with each study participant, one at baseline (T1) and the other at the end of the 6-month intervention period, 6 months after baseline (T2). Baseline data will be collected on socio-demographic, clinical, and primary and secondary outcome variables. Each assessment will take approximately 1.5 hours to complete. The Research Coordinator (RC) will meet regularly with the RAs to address questions and concerns and ensure consistency of approach across the sites. The RC will check the data throughout the data collection process to ensure minimal errors and missing data. Participant flow through the study will be illustrated using a flow diagram which conforms to the CONSORT guidelines [61] for reporting pragmatic trials (See Fig. 1).

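### The primary ANCOVA is valid and already uses baseline MCS, but excludes other likely baseline predictors; a short fixed covariate set would be a cheap, probably small gain in precision

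*Protocol article*

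**What the plan says.** The section on analysis of effectiveness in the protocol article gives each outcome its own ANCOVA, with 6-month change as the dependent variable, study group as the factor, "and the baseline value of the outcome as the covariate". The next paragraph says that an intention-to-treat "approach unadjusted for baseline characteristics will represent the primary analysis", with multiple imputation for missing data. Read together, the primary model for MCS contains arm and baseline MCS and nothing else.

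The data collection section says "Baseline data will be collected on socio-demographic, clinical, and primary and secondary outcome variables". Table 1 lists CES-D-10 and GAD-7 for older adults at T1. Number of chronic conditions is one of the three pre-selected subgroup factors, so it has to be recorded.

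Further adjustment appears only among the sensitivity analyses. One is a multivariable model, run if significant imbalances are found after randomization. The other adds site.

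**The concern.** Leaving out further baseline predictors is a stated choice, so it cannot be put down to detail that the article leaves to a fuller plan. A later plan that put them in the primary model would contradict the sentence.

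Two of the variables, CES-D-10 and GAD-7, are close in content to a mental component score. The Background section of the article itself links higher comorbidity burden to functional impairment and reduced quality of life. In a linear model, adjusting for a fixed set of baseline predictors leaves the type I error unchanged and keeps the mean difference as the estimand. To the extent that the predictors explain outcome variance beyond baseline MCS, it also narrows the confidence interval without new data.

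The planned multivariable sensitivity analysis does not serve that purpose. It is triggered by chance imbalance rather than by prognostic value, and it leaves the primary estimate as it is.

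**Working it through.** **Inputs from the Sample size section.** "MD = 3.68, SD=9.68", "two-sided alpha=0.05", 80% power, 20% attrition, with the method given as "PROC POWER, two-sample t-test for mean difference, equal variance, same sample size per group". The result is stated as "The target total sample size is 264 older adults".

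**1. Reproduce the plan's figure.** The standardised effect is 3.68 / 9.68 = 0.380. A two-sample t-test (noncentral t) then needs 110 per arm, or 220 evaluable. 220 × 1.2 = 264, which matches. With 20% attrition, 264 × 0.8 = 211.2 remain evaluable (105.6 per arm), a little under 220. Power there is 78.5%.

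**2. What the documents do not give.** Two quantities have to be assumed:
- the share of variance explained by the added covariates beyond baseline MCS (partial R²), taken here as 0.02 to 0.10;
- what the SD of 9.68 is. The section does not say whether it is a raw 6-month SD, a change SD or a residual SD after baseline MCS.

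**3. Effect on precision.** Residual SD after adding covariates = s₀ × √(1 − R²), where s₀ is the residual SD with baseline MCS alone. The proportional fall in the standard error does not depend on which SD 9.68 is. The equivalent extra sample is 211 / (1 − R²) − 211.

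Case A takes 9.68 as the residual SD, so s₀ = 9.68. The standard error is 9.68 × √(2/105.6) = 1.33, and the 95% half-width is 1.96 × 1.33 = 2.61 MCS points.

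Case B takes 9.68 as the raw 6-month SD with an assumed baseline correlation of 0.5, so s₀ = 9.68 × √(1 − 0.25) = 8.38. A change SD with the same correlation gives the same s₀, because the factor is then (1 + 0.5)/2 = 0.75.

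| Partial R² (assumed) | SE multiplier | Equivalent extra participants | Half-width, case A | Power, case A | Power, case B |
|---|---|---|---|---|---|
| 0 (plan as written) | 1.000 | 0 | 2.61 | 78.5% | 88.8% |
| 0.02 | 0.990 | 4 | 2.58 | 79.3% | 89.4% |
| 0.05 | 0.975 | 11 | 2.54 | 80.5% | 90.3% |
| 0.10 | 0.949 | 23 | 2.48 | 82.6% | 91.7% |

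For assumed baseline correlations from 0.4 to 0.7, power with baseline MCS alone runs from 85.1% to 97.1% if 9.68 is the raw SD, and from 90.8% down to 84.7% if it is the change SD.

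**4. How large could partial R² be?** Take one added covariate x, and assume that baseline MCS correlates 0.5 with 6-month MCS and 0.7 with x. If x correlates r with 6-month MCS, then

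partial R² = (r − 0.5 × 0.7)² / [(1 − 0.5²)(1 − 0.7²)] = (r − 0.35)² / 0.3825.

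This is 0.7% at r = 0.40, 2.6% at r = 0.45 and 5.9% at r = 0.50. The closer x is to baseline MCS in content, the less it adds.

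**5. Cost in degrees of freedom.** With 211 evaluable, the plan's model leaves 211 − 3 = 208. Three more covariates leave 205, which changes power by less than 0.01 percentage points.

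**The case against.** The strongest reply is that nothing here is wrong. The primary model is prespecified and unbiased, and it already includes baseline MCS, usually the strongest single predictor of the 6-month score. The sample size rests on a plain t-test and counts on no covariate gain, so no planning claim fails. A short model is also a legitimate preference. All of this stands, and it sets the severity.

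It is also true that the benefit is small in absolute terms. In case A the half-width shrinks by 0.03 to 0.13 MCS points (2.61 to 2.58, and 2.61 to 2.48) against a target difference of 3.68, which would rarely change a conclusion. What remains after the reply is that the gain needs no new data and costs almost nothing.

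A reader might infer three stronger things that the documents do not support:
- That the primary analysis ignores baseline altogether. The word unadjusted invites this, but the ANCOVA definition in the preceding paragraph puts baseline MCS in the model.
- That precision is shown to be lost. No correlation or R² is given, and overlap with baseline MCS could make the increment very small.
- That the extra covariates are needed to restore 80% power. That holds only if 9.68 is a residual SD and partial R² is about 0.05. In case B, power is already 88.8%.

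Site, the randomization stratum, is a separate question and is not part of this point.

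**Conclusion.** The point holds as a low-severity efficiency improvement. The primary analysis can be carried out as written without bias or inflated type I error. The documents fix it without covariates that are very likely available at baseline and plausibly prognostic, and the only wider adjustment is a conditional sensitivity analysis.

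The likely size is a 1–5% reduction in the standard error. In power terms this is roughly 1 to 4 percentage points if 9.68 is the residual SD, and 1 to 3 if it is the raw SD with a baseline correlation of 0.5. These figures rest on the assumed partial R² of 0.02 to 0.10, and the overlap calculation suggests that the lower part of that range should not be discounted.

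**What to change.** In the analysis section, replace the statement that the primary analysis is unadjusted with a named, fixed covariate set for the primary ANCOVA: baseline MCS, baseline CES-D-10, baseline GAD-7 and number of chronic conditions, used whatever imbalance is observed. Settle this before unblinding. Include the same variables in the imputation model, so that it is consistent with the analysis model. Report the model with baseline MCS alone as a sensitivity analysis, so that the analysis now planned stays visible.

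The cost is a sentence or two of wording, three degrees of freedom and a slightly longer model. No new data are needed. It would also help to state in the Sample size section which SD 9.68 is, since the baseline for any power statement depends on it.
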